**Participants**

The focus population of this trial are adolescent girls aged 15–18 years. The inclusion criteria are females: 1) aged 15–18 years; 2) living in the communities served by the selected community health centers; 3) with no HPV vaccination history, 4) with no prior allergies to vaccines; and 5) have a legal guardian who consents to participate the study. The exclusion criteria are females: 1) aged below 15 or above 18 years; 2) not living in the neighborhood served by the four community health centers; 3) received HPV vaccine(s); 4) ineligible to receive a vaccine based on clinical evaluation from a physician; or 5) a legal guardian refuses to consent to participate.

**Interventions**

*Pay-it-forward intervention arm*

Participants assigned in this arm will receive the following 1) an educational pamphlet about cervical cancer, HPV vaccination, and differences in common types of HPV vaccines; 2) information about the pay-it-forward vaccination program, including its purpose, the opportunity to receive postcard messages (details in the section of *Community engaged postcard messages*) and subsidized HPV vaccination, and the opportunity to voluntarily donate money towards someone else’s vaccine dose and write postcard messages. Participants will be told that the normal price to receive one dose of domestic 2v-HPV vaccine is RMB 329(US$ 49.78), and that previous participants donated money to cover the costs of the first dose of it along with postcard messages for them.

Participants (via caregivers) who agree to vaccinate can receive a vaccination on the same day of recruitment (when a girl is present) or make an appointment to visit again within the next three months for the administration of vaccination (when a girl is absent during the recruitment stage). After receiving a vaccination, girls, with caregivers or not, need to stay at the vaccination clinic for at least half-an-hour to observe any severe adverse events. During this period, research assistants will bring postcards and offer an opportunity to participants to donate and create handwritten messages for future participants. A donation/postcard collection box will be provided on-site, and a WeChat QR code will be provided to those who prefer an online donation to the program. WeChat is a multifunctional social mobile app embedded with monetary transaction functions. The donation will be anonymous, and project staff will be unaware of the donation amount. To link donations with other participant data, a postcard is assigned the same numerical ID of a participant and participants will be asked to put an intentional donation amount on the postcard along with their handwritten messages in the event of being willing to contribute. Neither the willingness to donate nor the amount of donation will affect their receiving the HPV vaccination services. The microdonations will be used to support future users. Donations and how these are used will be publicized periodically online via WeChat public accounts.

*Standard-of-care arm*

Participants assigned in this arm will be asked to pay out of pocket at the standard market price in the event of being willing to receive an HPV vaccination. The same educational pamphlet about cervical cancer, HPV vaccination, and types of HPV vaccines will be provided to participants in this arm, but they will not receive community-engaged messages or pay-it-forward information.

**Feasibility and acceptability pre-test**

We conducted a feasibility pre-test with 100 eligible girls and field-tested the trial implementation process from January 4, 2022 to February 18, 2022 in the urban study site [[21](https://bmcpublichealth.biomedcentral.com/articles/10.1186/s12889-022-14947-3#ref-CR21)]. We collected survey data about caregiver attitudes towards options of HPV vaccines, vaccine delay, and the pay-it forward intervention’s acceptability, appropriateness, and feasibility using adapted intervention measurements [[22](https://bmcpublichealth.biomedcentral.com/articles/10.1186/s12889-022-14947-3#ref-CR22)]. We organized a multi-stakeholder advisory meeting to discuss the pre-test results. These stakeholders were an HPV vaccination policymaker from Chengdu municipal health bureau, two public health practitioners in women and child health, two vaccine research experts, two global health researchers, and two infectious diseases researchers. We subsequently conducted four focus group discussions with a sub-set of participating caregivers (*n* = 21), and interviews with healthcare workers (n = 2) involved in the pre-test to better understand parental decision-making process for their daughter to receive HPV vaccination. The pre-test helped refine problem statement, sample size calculation, types of HPV vaccines to be provided in our trial, community-engaged postcard messages addressing knowledge gaps, and random sampling and recruitment strategies. These are described in detail below.

**Problem statement**

Our pre-test suggested that, due to the shortage of 4v and 9v-HPV vaccines in the market, the overwhelming majority of caregivers (91.5%) chose to delay their daughter’s HPV vaccination to wait for the above two types of vaccines to become available. This echoed a previous study [[11](https://bmcpublichealth.biomedcentral.com/articles/10.1186/s12889-022-14947-3#ref-CR11)] that there is greater demand for 4v and 9v-HPV vaccines than the currently available supply, but a delay or refusal of 2v-HPV vaccine uptake. A recent cohort study [[23](https://bmcpublichealth.biomedcentral.com/articles/10.1186/s12889-022-14947-3#ref-CR23)] demonstrated that 2v-HPV administered during the age of 12–13 years can reduce 87% of cervical cancer rates and 97% of grade 3 cervical intraepithelial neoplasia (CIN3), but such protection effects would significantly reduce for women receiving an vaccine at an older age, suggesting the importance of vaccination at an earlier age rather than later. The public health problem is therefore refined as how to address vaccine delay and increase *earlier* uptake of HPV vaccines that are currently available in the Chinese market among adolescent girls aged 15–18.

**Sample size calculation**

Our pre-test data showed that the pay-it-forward arm had an uptake rate of 98% (49/50) compared to 82% (41/50) in the standard-of-care arm. We, therefore, estimate a difference of 16% in vaccine uptake rates between the two arms. But because the current HPV vaccination rate among this population is generally low at around 10%, for the ongoing trial, we conservatively estimate an uptake rate of 20% in the standard-of-care arm and 36% in the pay-it-forward arm rather than the uptake rates in our pre-test. To achieve an 80% power to detect a difference between the two arms, 120 participants are needed respectively in the pay-it-forward and standard-of-care arms. The test statistic used is the two-sided unpooled Z test and calculated by PASS 2021. The significance level of the test is 0.05. Given a non-response and/or dropout rate of 10%, 133 participants for each arm are needed. To allow sub-analyses on secondary outcomes and sub-group analyses, we will increase the sample size by 20% to 160 in each arm (40 from each clinic in each arm), leading to a total of 320 participants.

**Types of HPV vaccines**

During the pre-test, we observed a substantial public demand for but an insufficient supply of 9v-HPV vaccine at the community health center. The center had to reserve the limited number of 9v-HPV vaccine for our pre-test participants, generating unintentional inequality of access to 9v-HPV vaccines between participants and not-participants. 4v-HPV vaccines were out-of-stock throughout the pre-test period. The advisory meeting revealed that the current supply of various types of HPV vaccines are insufficient to meet the demand in the next five to 10 years. Government-sponsored universal coverage of 4v and/or 9v-HPV vaccination for priority and catch-up groups (9–26 years) within the next decade in China is also unlikely. However, the supply of domestic 2v-HPV is relatively stable due to domestic pharmaceutical production lines. To ensure sufficient supply for all trial participants in the four study sites, we decided to use what is most available at the study sites (i.e., 2v-HPV vaccine). This may also help inform a cost-effective implementation strategy that complements future government-led schemes that use more accessible health products.

| **[figure not shown]** | **Title**: Do NOT let your child get infected (with HPV) due to a decision of waiting for a preferable HPV vaccine  **Slogan**: HPV vaccine. Cervical cancer is by far the only vaccine preventable cancer in the world.  **Text description**  **Key message:** The earlier, the younger, the better.  A British cohort study found that the younger age the HPV vaccination is, the better the protective effectiveness is.  Age of vaccine: 12-13 years; 14-16 years; 16-18 years  The incidence reduced by 87%; 62%; 34%  **Footnote bullets**  -After 9 years old, the earlier the vaccination is, the better the effectiveness is, get whatever HPV vaccines are available in the market. Earlier vaccination is more important than a 4vHPV/9vHPV.  -Experts suggest: do not miss the best vaccination age window because of waiting for a preferable vaccine. |
| **[figure not shown]** | **Title**: Do NOT let your child get infected (with HPV) due to a decision of waiting for a preferable HPV vaccine  **Slogan**: HPV vaccine. Cervical cancer is by far the only vaccine preventable cancer in the world.  **Text description**  Among the Chinese population, 84.5% of cervical cancer is caused by the two sub-types of HPV 16 and HPV 18. Bi-valent or 4vHPV vaccines can potentially reduce the odds by 85%, which is only 6% less than 9vHPV.  HPV vaccines and the HPV types protected against  Bi-valent: HPV 16 and 18  4vHPV: HPV 16, 18, 6 and 11  9vHPV: HPV 16, 18, 6, 11, 31, 33, 45, 52, and 58  **Footnote bullet**  Earlier vaccination is more important than a 4vHPV/9vHPV. |

**Random sampling and recruitment strategy**

Our pre-test recruited participants through a WeChat newsletter announcing the study to local residents living in the neighborhood and who are served by the community health center. This recruitment strategy was used because it is how the community health center announces updates about vaccine services to the residents. However, by reflecting on the high uptake rate in the standard-of-care arm, we speculate that this may be largely attributable to a biased sample recruited online and these participants were already interested in HPV vaccination. These participants were economically better off (62% of the caregivers had an annual family income of 80,000RMB or above), and better educated (78% obtained university or higher-level education) compared to the local average levels. In addition, eligible participants who did not subscribe to the newsletter of the community health center do not have equal odds to be reached by our trial compared to those who subscribed.

We revised the sampling strategy to a simple random sampling using the residential committee registration system. Specifically, we will obtain a de-identified contact list of adolescent girls aged 15–18 years from the residential committee via community health center staff. This list includes all girls of this age range living in the neighborhood who also registered their names and contacts at the community health center to receive relevant health services there. We will then conduct the simple random sampling of eligible girls via generating and assigning a random digit to each individual using Microsoft Excel. These individuals will then be sorted by the random digits from the smallest to the largest, and we will select individuals from the top of the list for telephone recruitment until we reach the expected sample size at each study site.

The community health center will send a short text message via the patient management platform of the community health center to inform caregivers of selected participants about a follow-up telephone call from our project staff in next few days. The telephone recruitment will be conducted using landlines of the community health centers. Our project staff will introduce the general project during the telephone call and obtain verbal consent. Consented caregivers and/or participants will be invited to visit the community health center for enrollment. We aim to recruit 80 eligible participants at each study site.

**Randomization and treatment allocation**

The research assistants will explain on-site the trial purpose, procedures, expected benefits and possible risks to participants, and obtain written consent to participate in the trial. Research assistants will then randomize participants into standard-of-care and pay-it-forward arms using a sealed envelope method. The envelope includes a random numerical ID generated using SPSS 21.0 that corresponds to the assigned arm (standard-of-care or pay-it-forward), a QR code for an online questionnaire survey, and postcard messages (pay-it-forward arm only). After receiving the allocated treatment, participants who agree to receive a vaccine will make an appointment through our trial and we will link them with a community health staff member who helps coordinate the administration of vaccination at the center.

We will use an information tracking sheet to record the assigned treatment, collect information about age (verified by identification card on-site), numerical ID and contact information. Personal information will be used for arranging clinical visits only and will not be accessible to staff who are not involved in the recruitment and clinical arrangement process.

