**Participation and consent**

Based on their assigned arm, participants will then be directed to research assistants who will deliver the allocated intervention. Participation in the study will be voluntary and anonymous. Access to other vaccination and medical services in the health center will not be affected in any way because of the participation in the study. Participants will be able to withdraw from the study at any time without giving any explanations.

All participants will be asked to complete a baseline survey after the consent. The questionnaires will collect information about their sociodemographic information, vaccine-related attitudes and behavior, pro-social intention and behavior, and their intended donation to support vaccination of other individuals (pay-it-forward arm only). We will add caregivers’ WeChat account for future follow-up and publicizing the microdonations and transparency.

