**Blinding**

In a behavioral intervention, both participants and people who deliver the treatment know which treatment they are receiving, and it is impossible to conduct a blind trial. But we will adopt several blinding techniques during the process to minimize biases. First, our trial will use an envelope concealment method. The process of generating the sequence of random digits and assembling envelopes is confidential to all on-site research assistants who recruit participants. Second, the allocated intervention will be concealed from study participants and research assistants onsite prior to assignment until they open the envelope. Second, the community health staff coordinator will not know which treatment a participant receives but only help coordinate within the clinic for administering the vaccination after the intervention delivery. Third, both the research assistants and/or community staff coordinator will help collect handwritten messages/donations, but they will be trained to maintain a high degree of consistency and neutrality in the process. Fourth, the allocated intervention (pay-it-forward or standard-of-care) will be blinded to physicians who prescribe an HPV vaccine throughout the process. Finally, the outcome assessors will be blinded from the knowledge of which intervention a participant receives.

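### Only pay-it-forward envelopes hold postcards, so concealment until opening is not secured; and the coordinator said not to know the arm may collect donations sought in one arm only

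*Supplement*

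**What the plan says.** All references are to protocol version 3.0 in the Supplement.

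**Envelopes.** Under Randomization and treatment allocation, staff explain the trial on site and take written consent. Then: "Research assistants will then randomize participants into standard-of-care and pay-it-forward arms using a sealed envelope method". Each envelope holds an ID number tied to the arm, a code for the online survey, "and postcard messages (pay-it-forward arm only"). The Blinding section claims that "the allocated intervention will be concealed from study participants and research assistants onsite prior to assignment until they open the envelope". In support it offers this: "The process of generating the sequence of random digits and assembling envelopes is confidential to all on-site research assistants who recruit participants". The envelopes are called sealed. Nothing is said about opacity, matched contents, outside numbering or order of use.

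**Coordinator.** The Blinding section states that "the community health staff coordinator will not know which treatment a participant receives". Its next sentence says that "both the research assistants and/or community staff coordinator will help collect handwritten messages/donations". Three other places tie these activities to one arm:
- Participation and consent limits to one arm the survey item on "their intended donation to support vaccination of other individuals (pay-it-forward arm only").
- Interventions describes giving and message-writing for the pay-it-forward arm only, during the observation period after vaccination, and names only research assistants for the task.
- The standard-of-care text says that arm gets neither the messages nor information about the program.

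Trial status records that data collection was complete when the protocol was updated on 4 May 2023.

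**The concern.** The protocol accepts that participants and those delivering the intervention cannot be blinded. Protection against selection bias then rests on nobody being able to foresee or choose the next allocation. An envelope with cards inside and one without are different objects. If staff can tell them apart, a family's apparent willingness or means could influence which envelope it gets, and the arms would no longer be comparable on the trait that most affects uptake.

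The coordinator issue is smaller. A person described as unaware of the arm is given a task that reveals it. A reader of the trial report would credit a blinding safeguard that the procedure does not guarantee.

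**Working it through.** **1. Envelopes: stated safeguards against each threat.** Contents in both arms: ID and survey code. Pay-it-forward only: postcards as well.

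- *Foreseeing the sequence from the list.* Covered: generation and assembly are kept from recruiting staff.
- *Opening early or reading through the paper.* Partly covered: sealed, but opacity is not stated.
- *Recognising the type by bulk or weight.* Not covered: no dummy card or matching is described.
- *Declining to enrol a family once the envelope is recognised.* Limited: families are randomly sampled from a registration list, and written consent precedes the envelope.
- *Taking another envelope or changing the order.* Not covered: no numbering, order of use or check is described.

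The gap is the combination of the third and fifth items.

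**2. Coordinator: order of events for one girl.** Consent; envelope opened; intervention delivered; family agrees to vaccinate; coordinator helps arrange it; first dose; observation period, when messages and donations are sought; later, second dose. First-dose uptake is the primary outcome and is already fixed when the collecting task reveals the arm. Second-dose completion, a secondary outcome, comes afterwards. So the blinding claim is contradicted, and any effect through this task is limited to what follows the first dose.

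**3. Size: purely illustrative.** The plan gives no figure for this point. The only plan figure used is the design difference, 36% − 20% = 16 points. The sample size built on it reproduces with the unpooled formula: (1.960 + 0.842)² × (0.20×0.80 + 0.36×0.64) / 0.16² = 119.7, that is 120 per arm as stated. The envelope point does not change it.

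Let *g* be the gap in uptake between keen and reluctant families, and *d* the excess share of keen families in the pay-it-forward arm. With no true effect, the false difference is *d* × *g*. None of the following inputs comes from the documents.

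- Assume *g* = 0.60 − 0.10 = 0.50.
- *d* = 0.05 gives 2.5 points; *d* = 0.10 gives 5 points.
- If a fraction *s* of each arm is exchanged keen for reluctant, *d* = 2*s*. Then *s* = 0.05 gives 5 points and *s* = 0.10 gives 10 points.
- With no steering, *d* = 0 and the bias is 0. If reluctant families are steered to the subsidy instead, the sign reverses.

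These scenarios run from −10 to +10 points and include zero. In absolute terms the non-zero values are 2.5/16 = 16% to 10/16 = 63% of the design difference.

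**The case against.** The case on the other side is substantial.

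- *Detectability is inferred.* The documents do not describe the envelopes' size, weight, stiffness or number of cards, and they refer to operating procedures that are not shown. This stands. One may say that the allocation may be detectable, not that it can be felt.
- *Other safeguards exist.* Random sampling and consent before opening limit selective enrolment. The model adjusts for site, income, education, marital status and caregiver sex. Outcomes come from administrative records, and assessors and prescribing physicians are said to be blinded. All true. But adjustment does not reach unmeasured willingness, and blinded assessment protects measurement, not who enters each arm.
- *The coordinator's part is optional.* The wording allows that only research assistants collect. That softens the contradiction but does not remove it, because the text still permits the coordinator to do so.

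A reader might infer four stronger points that the documents do not support.

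- *The coordinator could influence first-dose uptake.* Donations follow that dose, so the task cannot do this for the same girl. The tracking sheet that records the arm is not said to be open to the coordinator, nor clearly closed, so it does not establish the point either.
- *Any error must favour the intervention.* Staff might as readily give the subsidy to poorer or reluctant families.
- *The outcome is settled at the enrolment visit.* Version 3.0 allows an appointment within three months.
- *Allocation was actually subverted.* Nothing in the documents shows it.

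**Conclusion.** The point holds in two limited parts. First, the arms' envelopes differ in content by design, and no stated safeguard addresses that difference, so concealment until opening is claimed but not secured. The remaining route is swapping or re-ordering envelopes after consent. Whether it was used, in which direction and to what extent is unknown; the figures above only show that modest steering would not be negligible beside 16 points. This part assumes that the unseen operating procedures did not match the envelopes.

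Second, the coordinator-blinding claim is contradicted by the sentence after it. The consequence is a blinding statement that cannot be relied on, with possible relevance to second-dose completion and none, through this task, to that girl's first-dose uptake.

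Both parts deserve correction. Neither invalidates the trial.

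**What to change.** **As design.** Use identical, opaque, sequentially numbered envelopes taken in order, either with blank cards of the same size in the standard-of-care envelopes or with postcards handed out only after opening. Let only research assistants collect messages and donations, or delete the claim that the coordinator does not know the arm. The cost is a few hundred blank cards and one reassigned task.

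**Now that data collection is complete.**
- Report how the envelopes were built, stored and used, including any matching done under the operating procedures.
- Compare the allocation sequence with enrolment order by site, where the records allow. The protocol mentions only a random ID, so an ordered list may not exist; if so, say so.
- Show balance by arm within site on fixed characteristics such as caregiver sex, education and household income. Attitude items are a weaker check, because the survey code is inside the envelope and the answers may follow knowledge of the arm.
- State who collected messages and donations.
- Withdraw any concealment or blinding claim that the procedure did not support.

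This costs some wording, one check of the sequence and one balance table, with no extra staff.
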